##### Sleep parameters

2.6.2.2

Sleep parameters, including total sleep time (TST), sleep onset latency, number of awakenings, wake after sleep onset duration, and sleep efficiency (i.e., the ratio between TST and time in bed), will be recorded with the Consensus Sleep Diary (CSD) and an actigraph. The CSD is a self-report table in which the participant reports his sleep-related behaviors, including time and duration.^[68]^ The CSD has been validated in an insomnia disorder population. An actigraph is a device, usually wrist worn, capable of measuring gross motor activity. Sleep parameters can be calculated by software using the 24-hour gross motor activity measured by the actigraph. In this study, we will use the readiband (Fatigue Science, Canada), which has been validated against polysomnography.^[69]^ The sleep parameters will be averaged on one week if at least 4 days of data are available.

##### Expectancy, adherence and acceptability

2.6.2.3

Outcome expectancy will be measured with the Credibility and Expectancy Questionnaire (CEQ). This questionnaire was developed in 1972 to assess the credibility of placebo behavioral interventions.^[70]^ The revised version of the questionnaire has acceptable psychometric properties ^[71,72]^ and has been widely used to assess expectancy in clinical trials. The count of the unused capsules collected during the third visit will serve as estimation for adherence, which will be also monitored with the CSD. The third item of the CEQ will be used to assess acceptability.

##### Baseline assessments

2.6.2.4

Besides the outcome measurements, life events and night pain levels will be collected at baseline in order to assess the influence of these measures on the outcomes. Life events will be assessed with the List of Threatening Events (LTE), a list of 12 life-event categories with considerable long-term contextual threat.^[73]^ The LTE has acceptable psychometric properties.^[74]^ Night pain levels will be assessed with a 100° pain visual analog scale (VAS), adapted for the circumstances with the question: “what is your average pain level when you are trying to sleep?” The VAS is a valid and sensitive instrument to assess pain levels.^[75,76]^

### Clinical significance

2.7

A decrease of 7 points in the ISI score was found to be an indicator of moderate improvement for insomnia disorder.^[62]^ Therefore, a decrease of 7 points or more in the ISI score at post-treatment compared to pre-treatment will be considered clinically significant.

### Data collection and management

2.8

Electronic data will be collected with Research Electronic Data Capture (REDCap) database. REDCap surveys utilize a secure connection to the server for data collection which does not record IP addresses of participants. The questionnaires will be completed by the participant on REDCap via an iPad during the 3 face-to-face visits and by the investigator during the mid-treatment and follow-up phone interviews according to the participant's oral answers. A secured link to the database for the CSD will be sent every day via email to the participant. Paper forms for the sleep diary will be offered as an option for those who prefer them. For the follow-up, these will be supplied along with reply paid envelopes. Electronic data will be stored in REDCap for the duration of the trial and paper data will be stored in a locked cabinet at the trial site. Personal information will be kept in REDCap and an excel file protected with a password before and during the trial, and in a masterlist stored in a shared drive with restricted access after the trial. The final trial dataset will be accessible only to the investigators. In order to avoid missing data, the importance of complete data collection will be emphasized at enrolment and participants who withdraw from the study will be asked to complete the data collection, if willing. The research team will monitor data on an ongoing basis.

### Statistical analysis

2.9

Continuous data will be analyzed with linear mixed effects model, the data being corrected for baseline characteristics; mean, standard deviation, effect size, 95% CI and *P*-value will be reported. Dichotomous data will be analyzed with Chi-square and counts, percentages, and *P*-value will be reported. We will analyze the final vale of the outcomes with a significance level of α=0.05. Both an intention-to-treat analysis and a per-protocol analysis will be conducted, the intention-to-treat analysis being of primary interest as it reflects better the effectiveness of the investigational product. The effect of expectancy and CM diagnosis on the trial outcomes will also be analyzed. The statistical analysis will be performed with SPSS 25 (IBM).

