Zao Ren An Shen (ZRAS) is a CHM formula composed of 3 herbs, that is, Suan Zao Ren (Ziziphi Spinosae Semen), Wu Wei Zi (Schisandrae Chinensis Fructus) and Dan shen (Salviae Miltiorrhizae Radix et Rhizoma), which have all sedative effects and low toxicity.^[34–41]^ This formula, manufactured in the forms of capsule, granule and solution, is indicated for insomnia.^[42]^ Clinical trials on ZRAS have showed a better effect than placebo and a similar or better effect than BzRAs.^[43–57]^ Adverse events were also less reported by participant taking ZRAS compared to BzRAs.^[43,44,47–51,53,54,56,57]^ However, none of these studies used appropriate methods of randomization and blinding. There is a need for high-quality RCTs.

The objective of this study is to assess the efficacy and the safety of Zao Ren An Shen capsule compared to placebo for chronic insomnia. As ZRAS is proposed as an alternative treatment and not a first-line treatment, we will use placebo as a comparator with a superiority framework. The primary outcomes are insomnia severity measured with the Insomnia Severity Index (ISI) for efficacy and the number of adverse events (AEs) for safety. The primary endpoint is post-treatment (week 4). We hypothesize that ZRAS capsule will show a better efficacy than and a similar safety to placebo. Secondary outcomes include objective and subjective sleep parameters, fatigue levels, psychological status, quality of life, adherence, and acceptability. The secondary endpoints are mid-treatment (week 2) and follow-up (week 8).

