### Sample size

2.10

The standard deviation of the ISI total score in an insomnia population is 4.1.^[61]^ A difference of 7 points between baseline and post-treatment is considered as clinically significant.^[62]^ As placebo would give a decrease of approximately 4 points,^[78]^ the difference between the 2 groups at post-treatment has to be of 0.73 standard deviations. Using a 0.05 significance level, 90% power and allowing for 10% dropout rate, a sample size of 90 participants, 45 in each group, will be required.

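### Section 2.9 fixes an unadjusted chi-square for dichotomous data, so any comparison on the 7-point ISI fall would ignore baseline ISI and lose some power

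*Protocol article*

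**What the plan says.** Section 2.9 treats the two kinds of outcome differently. For continuous outcomes: "Continuous data will be analyzed with linear mixed effects model, the data being corrected for baseline characteristics", with an effect size and 95% CI among the results to be reported. For yes/no outcomes: "Dichotomous data will be analyzed with Chi-square", and counts, percentages and a P-value are all that is promised. The same section runs intention-to-treat and per-protocol analyses, "the intention-to-treat analysis being of primary interest as it reflects better the effectiveness of the investigational product".

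Section 2.7 states that "a decrease of 7 points or more in the ISI score at post-treatment compared to pre-treatment will be considered clinically significant". The introduction names the main efficacy measure: "The primary outcomes are insomnia severity measured with the Insomnia Severity Index (ISI) for efficacy". The 7-point fall is not in its list of primary or secondary outcomes. Section 2.10 uses the same 7 points to derive the sample size, "allowing for 10% dropout rate". Section 2.8 asks participants who withdraw to go on giving data if they are willing.

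**The concern.** The 7-point fall is the only evident yes/no efficacy criterion in the article, so the chi-square sentence would govern any comparison of the arms on it. The criterion is a change from baseline, and how hard it is to meet depends on where the participant starts. The minimum entry score is 10 (section 2.3.3). From there a 7-point fall means 10 − 7 = 3 or less on a 0 to 28 scale, whereas from 24 it means 24 − 7 = 17. Baseline ISI is collected for everyone and would be a strong covariate, and the plan already uses baseline correction for the continuous outcomes. The chi-square cannot use it.

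Readers would probably judge the plan's own threshold of clinical significance by the proportion in each arm who reach it. Randomisation of 90 participants is unstratified (section 2.4), so an adjusted analysis would also give an estimate less moved by chance differences in baseline severity.

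**Working it through.** **The plan's own sample size.** Inputs from section 2.10: falls of 7 and 4 points, SD 4.1, alpha 0.05 (taken as two-sided), power 90%, dropout 10%.
- Effect: (7 − 4)/4.1 = 0.73 SD.
- Per arm: 2 × (1.960 + 1.282)² / (3/4.1)² = 39.3, rounded up to 40.
- With dropout: 40/0.9 = 44.4, rounded up to 45 per arm, 90 in total. This matches the plan. It is sized for the continuous score.

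**What those figures imply for the 7-point criterion.** Take the change score as normal. Its SD is 4.1 × √(2(1 − r)), where r is the baseline to week-4 correlation, which the article does not give. At r = 0.5 the SD of change is 4.1.
- Active: 1 − Φ((7 − 7)/4.1) = 50.0%.
- Placebo: 1 − Φ((7 − 4)/4.1) = 23.2%.
- Chi-square power: 76% with 45 per arm, 71% with 40.5 per arm (45 × 0.9).
- If the SD of change runs from 3.2 to 5.8, power with 40.5 per arm runs from 89% down to 44%.

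**What leaving out baseline costs.** Simulated trials had 45 per arm, whole-number ISI scores, baseline SD 4.1 cut at 10, week-4 SD about 4.1, falls of 4 and 7 points, and 10% dropout at random. Both tests used the same participants with a week-4 score, so the difference comes from the covariate alone.

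| Correlation | Chi-square → logistic with baseline ISI; baseline mean 18, Wald test, 3000 trials | Same; baseline mean 17, likelihood-ratio test, 4000 trials |
|---|---|---|
| 0.3 | 60% → 68% | 59% → 70% |
| 0.5 | 73% → 79% | 74% → 81% |
| 0.6 | 82% → 85% | not run |
| 0.7 | not run | 91% → 94% |

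In the right-hand column the cut at 10 leaves the achieved correlation a little below the nominal one. A further check set the correlation after the cut and used 6000 trials at each of means 17 and 18. Wald-test gains were about 8 points at 0.3, 3 to 4 at 0.5 and 1 at 0.7. The likelihood-ratio test gave 9 to 10, 5, and 1 to 2.

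**Validity.** With no treatment effect, the 4000-trial set-up rejected in 4.4% to 6.2% of trials across all the tests. The chi-square is valid; it is merely less efficient.

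**Does excluding dropouts explain the lost power?** No. In the 4000-trial set-up at r = 0.5, counting dropouts as not reaching the fall takes the chi-square from 74% to 72%, and the adjusted analysis from 81% to 77%.

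**The case against.** The strongest reply is that no comparison of responders is promised. Section 2.7 can be read as a threshold for interpreting the result, section 2.10 uses the 7 points at group level, and the introduction lists no such outcome. That stands, and the point is therefore conditional: it applies if the arms are compared on the criterion.

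A second reply is that an unadjusted chi-square is a valid test and that adjustment is a matter of efficiency. That is also right. The point is that the plan fixes the weaker of two analyses although the covariate is at hand.

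A reader might infer something stronger: that about 9 dropouts (10% of 90) will lack a week-4 score, that the chi-square drops them, and that the intention-to-treat comparison becomes a completers-only one that loses power. The article does not support this.
- A chi-square excludes nobody by itself. It can be run on all 90 once missing scores are classified or imputed, and nothing in the article excludes dropouts.
- Dropout need not mean a missing score, because section 2.8 seeks data after withdrawal.
- The rule for a missing derived variable is detail that a full protocol or SAP may hold.
- Bias could go either way. Take illustrative rates of 53% and 27% among those observed (a 26-point difference) and suppose that dropouts do not improve. Dropout of 15% on active and 5% on placebo gives 0.53 × 0.85 − 0.27 × 0.95 = 19 points. The reverse gives 0.53 × 0.95 − 0.27 × 0.85 = 27 points. The article supports neither split.

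**Conclusion.** The point holds in a limited form. Section 2.9 corrects continuous outcomes for baseline and fixes an uncorrected test for yes/no outcomes, and the 7-point ISI fall depends on baseline ISI. For a comparison on that criterion the cost is about 1 to 8 points of power over correlations of 0.3 to 0.7. A likelihood-ratio test puts the upper end at about 10 or 11. The correlation, the baseline mean of 17 to 18 and dropout at random are assumptions. The falls, the SD and the dropout rate are the plan's.

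The primary comparison of ISI scores by mixed model, and the sample size built on it, are not affected. This is a cheap improvement to a supporting analysis and not a threat to the trial's main conclusion.

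**What to change.** In section 2.9, state that any comparison on the 7-point ISI criterion will use logistic regression on treatment with baseline ISI as covariate, in the intention-to-treat set. Report the risk difference with its 95% CI beside the counts and percentages.

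As a supporting step, handle a missing week-4 ISI by multiple imputation from baseline and mid-treatment ISI. Add one sensitivity analysis that counts such participants as not reaching the fall. This keeps everyone randomised in the analysis and guards against bias; it should not be presented as a gain in power.

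The cost is a sentence or two of text and a little more analysis work, with no new data. The estimate becomes model-based, and the risk difference has to be derived from the fitted model instead of read from a two-by-two table.

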### Sample size

2.10

The standard deviation of the ISI total score in an insomnia population is 4.1.^[61]^ A difference of 7 points between baseline and post-treatment is considered as clinically significant.^[62]^ As placebo would give a decrease of approximately 4 points,^[78]^ the difference between the 2 groups at post-treatment has to be of 0.73 standard deviations. Using a 0.05 significance level, 90% power and allowing for 10% dropout rate, a sample size of 90 participants, 45 in each group, will be required.

## Discussion

3

The objective of this study is to assess if ZRAS is relatively safe and effective for chronic insomnia compared to placebo. This study, which has a stringent design with randomization and double blinding, will provide high-quality evidence for or against the use of ZRAS capsule as an alternative treatment for chronic insomnia.

If the hypothesis is verified (i.e., ZRAS is relatively safe and more effective than placebo), ZRAS may be recommended if the current recommended treatments (i.e., pharmacotherapy and CBT-I) are ineffective, not available or if the patient refuses these treatments. More RCTs comparing ZRAS capsule to pharmacotherapy or CBT-I would be also needed to assess if ZRAS should be used as a first line or alternative treatment. RCTs comparing ZRAS capsule in addition to recommended treatments to recommended treatments alone would help us to understand the value of adding ZRAS capsule to these treatments.

The strengths of this study are:

The use of a third-party randomization scheme with allocation concealment and double blinding.The use of a placebo similar in appearance and taste to the active.The combination of subjective (i.e., with the CSD) and objective (i.e., with actigraphy) measures of sleep.A comprehensive assessment encompassing fatigue, psychological status, quality of life, satisfaction and acceptability.The use of a CM diagnosis.
